##### Secondary endpoints

The patient is successfully able to be planned at the assigned dose level.Quality of life, assessed with the Functional Assessment of Cancer Therapy: General (FACT-G) and the EuroQol 5 Dimension, 5 Level (EQ-5D-5L)Time to development of new metastatic lesionsProgression-free survival, defined as time from randomization to disease progression at any site or deathOverall survival, defined as time from randomization to death from any cause

#### Patient selection

##### Inclusion criteria

Age 18 or olderWilling and able to provide informed consentEastern Cooperative Oncology Group (ECOG) performance status 0–2Life expectancy > 3 monthsHistologically confirmed malignancy with metastatic disease detected on imaging. A biopsy of a metastatic site is preferred, but not requiredPresence of polymetastatic disease, defined as total number of lesions greater than 10No standard of care systemic therapy option exists for the patient, the patient refuses further standard systemic therapy, or there is no intent to deliver systemic therapy for 3 months after enrollmentAt the discretion of the treating oncologist, it is believed that all sites of disease can be safely planned and treated

##### Exclusion criteria

Serious medical comorbidities precluding radiotherapy. These include interstitial lung disease in patients receiving lung radiotherapy, Chron’s disease in patients where the gastrointestinal tract will receive radiotherapy, ulcerative colitis where the bowel will receive radiotherapy, or connective tissue disorders such as lupus or scleroderma.For patients with liver metastases, moderate/severe liver dysfunction (Child Pugh B or C)Inadequate baseline bone marrow function (i.e. symptomatic anemia, neutropenia and/or thrombocytopenia which may interfere with the ability to deliver radiotherapy)Chronic kidney dysfunction (eGFR less than 30) where a significant dose of radiation is expected to be delivered to the kidneys.Substantial overlap with a previously treated radiation volume. Prior radiotherapy in general is allowed, as long as the composite plan meets dose constraints herein. For patients treated with radiation previously, biologically effective dose calculations should be used to equate previous doses to the tolerances doses listed in Additional file 1.Prior treatment with systemic radiopharmaceuticals (i.e. Radium-223 or Lutetium-177)Any single lesion greater than 5 cm in size.More than 50 metastases (count excluding equivocal lesions < 5 mm in size)Any brain metastasis greater than 3 cm in size, or a total volume of brain metastases greater than 30 cc.Polymetastatic cancer limited to the brain.Brainstem metastases.Evidence of epidural disease on baseline imaging.Clinical or radiologic evidence of spinal cord compression.Dominant brain metastasis requiring surgical decompression.Inability to treat all sites of disease, which may include disease involving the gastrointestinal tract, mesenteric lymph nodes, or skin. This may also include diffuse/miliary metastatic disease (i.e. brain, bone, lung, liver) or other sites where it would be impossible to deliver radiotherapy at the intended dose level (i.e. lymphangitic spread, malignancy pleural effusion/ascites, leptomeningeal metastases).Systemic therapy use 2 weeks prior to radiotherapy delivery.Pregnant or lactating women.

#### Pre-treatment evaluation

History and Physical examination, including prior cancer therapies.Restaging within 6 weeks prior to enrolment:Brain: CT or MRI for tumour sites with propensity for brain metastases. All patients with brain metastases (at enrolment or previously treated) require an MRI of the brain.Body: CT neck/chest/abdomen/pelvis and bone scan is required. This may be replaced or supplemented with an appropriate PET/CT (i.e. 18-FDG or PSMA) for tumours where uptake is expected.Additional imaging as clinically indicatedComplete blood count (Hemoglobin, white blood cell count, absolute neutrophil count, platelets).CreatinineLiver function tests (AST, ALT, GGT, alkaline phosphatase), albumin, bilirubin and INR for patients with liver metastases.Pregnancy test for women of child-bearing age.Completion of FACT-G and EQ-5D-5L quality of life forms.Radiotherapy treatment plan has been reviewed by a physicist or radiation oncologist.

#### Data collection

All study data will be entered electronically into REDCap. Any de-identified source documents may be uploaded directly into REDCap for data entry and analysis.

#### Treatment plan

SABR in will be delivered with three major guiding principles:
**Minimization of Toxicity**. The radiotherapy doses used herein are lower than those used for radical treatments, and normal tissue tolerance doses will never be exceeded. Concurrent chemotherapy or targeted therapy at the time of radiotherapy (other than conventional hormone-based therapies which may continue) is not permitted. The starting dose for this trial will by 12Gy in 2 fractions with each fraction given weekly, a dose expected to be safe and well-tolerated based on prior clinical experience with hemi-body radiation.2.**Minimization of Treatment Burden**. To avoid excessive treatment delivery time and treatment burden, radiotherapy is to be delivered using a limited number of isocentres. Given the volumes to be treated, a given “fraction” may require treatment over 1–3 days to keep daily treatment times tolerable. The smallest number of isocentres will be used and will be limited to three isocentres treated per treatment day. A maximum of three treatment days are to be utilized per dose level (i.e. three treatment days per week maximum) for a maximum of 9 isocentres per fraction. For example, a patient requiring treatment of polymetastatic disease involving the brain, lung and abdomen might require a given fraction to be delivered over 3 consecutive days: day 1, up to 3 isocentres to cover head, neck and upper thorax; day 2, up to 3 isocentres to cover lower thorax and upper abdomen; day 3, up to 3 isocentres to cover lower abdomen and pelvis.3.**Strict adherence to dose constraints**. If a patient undergoes planning but cannot be treated at the current dose level they will receive treatment at the next highest dose level that can be safely planned. These patients will still be followed as per the clinical trial, and toxicity will be recorded. The phase 1 3 + 3 dose escalation evaluation will only apply to those who can have a safe radiotherapy treatment plan created at the target dose level. For example, a patient who fails planning at 30Gy in 5 fractions but who has a radiation plan meeting dose constraints at 18gy in 3 fractions will be treated at the lower dose level (and counted as a treatment planning failure at the higher dose level)

The fraction size throughout the study will remain at 6 Gy per fraction with dose constraints as outlined in Additional file 1. Each fraction must be completed within 3 treatment days and 1 calendar week. Dose escalation will proceed as follows, starting at Level 1; dose level 0 exists for those patients who fail planning at even dose level I and is deemed safe (based on the body of literature demonstrating safe delivery of 6Gy hemi-body radiation without conformal delivery):

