##### Dose escalation criteria

For a given dose level, toxicity as DLT will be assessed after three patients have been treated at a given dose level at the 6-week assessment post treatment. If all three patients meet the co-primary safety endpoint, escalation to the next dose level will occur. If two or three patients fail the co-primary safety endpoint, the MTD will be determined as the dose level preceding the failed dose level. If one patient fails the co-primary safety endpoint, an additional three patients will be accrued at that dose level. If one or more of these additional three patients fail the co-primary safety endpoint, the MTD will be determined as the dose level preceding the failed dose level. If all three additional patients meet the co-primary safety endpoint (i.e. a cumulative five of six patients pass the co-primary safety endpoint), dose escalation to the next level will occur. All patients at a given dose level must be assessed for 6-week toxicity before escalation to the next dose level can occur.

Treatment planning futility will be considered if less than 33% of the patients (to a maximum of 9 patients) at a specific dose level can successfully have a treatment plan generated for that dose level meeting organ at risk constraints. If treatment planning futility is encountered, the MTD will be considered as the dose level preceding the failed dose level.

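### The MTD can rest on three patients, or on none at dose level 0, and the decision rule leaves out toxicity recorded in patients treated at the same dose after a planning failure

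*Protocol article*

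**What the plan says.** Under Dose escalation criteria, three patients are assessed six weeks after treatment. "If all three patients meet the co-primary safety endpoint, escalation to the next dose level will occur". "If one patient fails the co-primary safety endpoint, an additional three patients will be accrued at that dose level", and one further failure among those three fails the level. "If two or three patients fail the co-primary safety endpoint, the MTD will be determined as the dose level preceding the failed dose level". Planning can fail a level too: "If treatment planning futility is encountered, the MTD will be considered as the dose level preceding the failed dose level". Neither route asks for more patients at the level that is then named.

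Under Treatment plan, a patient who cannot be planned at the assigned level is treated at a lower level that can be planned. "These patients will still be followed as per the clinical trial, and toxicity will be recorded". The next sentence says that the "dose escalation evaluation will only apply to those who can have a safe radiotherapy treatment plan created at the target dose level". The Treatment planning section repeats that a planning failure does not enter the 3 + 3 study.

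Level 0 is listed apart from the four escalation levels: "dose level 0 exists for those patients who fail planning at even dose level I and is deemed safe", on the strength of hemi-body literature. Treatment starts at level 1.

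**The concern.** Excluding a patient from the evaluation of a dose that the patient never received is sensible. The difficulty lies at the dose the patient did receive. Suppose level 3 is cleared on 0/3, level 4 opens, several patients fail planning there and are treated at level 3, and level 4 then fails. Level 3 becomes the MTD on its three original patients. The later patients had the same dose and a recorded six-week assessment, yet no rule reopens level 3 in the light of their outcomes.

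If level 1 fails, the preceding level is level 0. Its only patients would be planning failures from higher levels, whom the 3 + 3 excludes.

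Establishing the MTD is how the protocol meets its objective, and the abstract says that the MTD is for exploration in future studies. Following the plan exactly could put forward a dose that its own same-dose data contradict, or a dose with no evaluated cohort.

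**Working it through.** **The plan's own figure.** Maximum accrual is 4 levels × 12 = 48, which reproduces. It covers levels 1–4 only, with no allowance for a level 0 cohort.

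**Assumptions.** The protocol states no target or expected failure rate, so the rates p below are assumed and shown as a range. Planning futility is ignored in the probabilities.

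**1. What 0/3 shows.** The exact (Clopper-Pearson) two-sided 95% upper limit for 0 of n is 1 − 0.025^(1/n).
- 0/3: 1 − 0.025^(1/3) = 70.8%
- 0/6: 45.9%
- 0/9: 33.6%

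**2. Chance that a level is cleared.** P(clear) = (1−p)³ + 3p(1−p)² × (1−p)³. The first term is clearance on three patients.
- p = 30%: 49.4%, of which 34.3 points on three patients
- p = 40%: 30.9%, of which 21.6 points on three patients

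**3. How often an MTD at levels 1–3 rests on three patients.** Chaining this formula over levels 1–4 gives, as a share of all MTDs named at levels 1–3:

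| Assumed failure rates, levels 1–4 | Share resting on three |
|---|---|
| 5/10/20/30% | 78% |
| 10/20/30/40% | 74% |
| 10% at every level | 81% |
| 20/30/40/50% | 71% |
| 30/40/50/60% | 70% |

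**4. How often the rule points to level 0.** This is 1 − P(clear) at level 1.
- p = 5%: 1 − (0.857 + 0.116) = 2.7%
- p = 10%: 1 − (0.729 + 0.177) = 9.4%
- p = 15%: 1 − (0.614 + 0.200) = 18.6%

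**5. How many same-dose patients may be left out.** Planning futility is success below 33%, judged on at most 9 patients. Three of nine is 33.3% and not futile, so 9 − 3 = 6 can step down. At 2/9 or fewer, 7 to 9 step down. These are maxima for any one lower level, because a patient may drop by more than one level.

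**6. Whether those outcomes could matter.** The plan fails a level at two failures in six, one third. Take a level cleared on 0/3 and six stepped-down patients who all land on it. The pooled rate reaches one third at 3/9 (exact 95% interval 7.5–70.1%), so three or more of the six must fail.

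| True failure rate in the six | P(3 or more of 6 fail) |
|---|---|
| 20% | 9.9% |
| 30% | 25.6% |
| 40% | 45.6% |
| 50% | 65.6% |

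In each of these cases the rule as written would leave the MTD unchanged.

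**The case against.** **The rule is complete and conventional in kind.** That is fair. A 3 + 3 gives wide intervals by nature, and this protocol never promises six patients at the MTD. A reader might infer that six evaluable patients is the plan's own standard. It is not: five of six passing applies only after exactly one failure in the first three. A required expansion to six would be a design preference, and this point does not rest on it.

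**The stepped-down data are not lost.** This stands in part. The monitoring committee reviews the chart of every grade 4–5 case, with no exception for stepped-down patients, and may recommend dose adjustment or stopping. The Analysis plan also describes six-week toxicity. But the committee meets annually, acts at its discretion and does not set the MTD. It does not apply the composite endpoint, which also counts treatment completion and multiple grade 3 events.

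**Stepped-down patients might be thought to count at the lower level, since they have a safe plan there.** The text does not support this. The Treatment planning section keeps them out of the 3 + 3 study, and a level's evaluation is finished before the next one opens.

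**A reader might infer that the exclusion makes the MTD look safer than it is.** The documents do not show this. Stepped-down patients must meet the same dose constraints, and the Background suggests that toxicity may depend mainly on organ dose. The Discussion says that lesion distribution, size and proximity to organs matter for how many lesions can be treated safely, so a difference is plausible, but its direction is unknown.

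**Level 0 as MTD is an inference.** True: Dose escalation criteria never names level 0. It is, however, the only level below level 1, and no other outcome is given for a failed level 1.

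**Conclusion.** The point holds in this form. The rule can name an MTD on three evaluated patients, or point to level 0 with none. It also shuts out recorded outcomes at that same dose, apart from discretionary review of grade 4–5 events.

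Under the assumed rates, 70–81% of MTDs at levels 1–3 rest on three patients, and level 0 is reached in about 3–19% of trials when level 1 fails in 5–15% of patients. Six stepped-down patients, twice the number counted, can arise without planning futility, and more with it. How many would land on the level named MTD cannot be derived from the document.

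A larger headline is tempting. With rates of 5/10/20/33%, about 76% of trials end on a level with at most three escalation patients. That total includes 19% in which level 4 itself clears on three, where no level failed and the preceding-level rule was never used. The part due to that rule is about 54% + 3% = 57%. The case for change rests on the unused same-dose data and the unevaluated level 0, since the small cohort alone is a known feature of the design.

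**What to change.** 1. Keep stepped-down patients out of the evaluation of the level they did not receive. Before naming an MTD, assess the co-primary safety endpoint in all patients treated at that dose. Judge completion against the dose level actually planned, because the present criterion refers to the assigned level and is unclear for these patients. Show results pooled and separately for 3 + 3 and stepped-down patients, with exact confidence intervals. If the pooled result meets the plan's own failure criterion (two in six, that is one third or more), do not name that level on the 3 + 3 patients alone. The sponsor must reconcile Treatment plan, Treatment planning and Dose escalation criteria and state what follows.

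2. If level 1 fails, report that no MTD was established among the levels evaluated, rather than naming level 0 by default. Reconcile the description of level 0 under Treatment plan with Dose escalation criteria.

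Both changes need wording only, use data already collected and add no patients. The cost is a possibly less definite MTD conclusion and a pooled group that is more mixed anatomically, which is why the two groups should also be shown apart.

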##### De-escalation dose level

Dose level 0: 6Gy × 1 fraction to all sites in 1 week.

##### Escalation dose levels

Dose level 1: 6Gy × 2 fractions to all sites in 2 weeks.

Dose level 2: 6Gy × 3 fractions to all sites in 3 weeks.

Dose level 3: 6Gy × 4 fractions to all sites in 4 weeks.

Dose level 4: 6Gy × 5 fractions to all sites in 5 weeks.

If treatment at the accrued dose level cannot be planned safely, then the next lowest dose level will be attempted to be planned and delivered to the patient if it can meet organ at risk (OAR) constraints and target coverage goals. For example, if radiation cannot safely be planned at dose level 1, then dose level 0 will be attempted to be planned. For higher dose levels, multiple de-escalations can be planned until a dosimetrically safe plan is generated.

##### Target definition

The maximum number of targets will be 50, excluding indeterminate lesions. For patients with lymph node metastases, a targetable lesion will be considered as a lymph node > 10 mm in short axis or with radiographic features strongly suspicious for metastatic involvement (i.e. presence of necrosis, uptake of radiotracer in PET). Lung metastases will be considered for treatment when the short axis is > 8 mm or radiographic features are strongly suspicious for metastatic involvement (i.e. uptake of radiotracer in PET).

Targets which have previously been treated with ablative or palliative therapies (i.e. SABR, palliative radiotherapy, radiofrequency ablation, or surgery) shall not be counted unless there is unequivocal progression on baseline imaging.

Patients who have small indeterminate nodules (i.e. a 3 mm lung nodule) will not have these lesions count towards the number of target lesions and will not be targeted with SABR.

##### Simulation and immobilization

Patients will be simulated using a fast helical CT scan through the entire body, at minimum vertex of the skull to the mid femur. If there is disease below the lesser trochanter, a separate CT simulation of the lower extremities (from the top of femoral head to the bottom of the feet) will be used for treatment planning. Immobilization will be with a thermoplastic shell with arms down, a position that has been shown to be safe for lung radiotherapy [21]. Total body stereotactic immobilization is allowed.

An additional 4D-CT scan is mandatory for targets within the thorax and upper abdomen. Where indicated and tolerable, gating (preferably with a wide duty cycle) or deep inspiration breath hold will be utilized for respiratory motion management in the thorax and upper abdomen. In cases where gating or DIBH are not tolerable, a free breathing delivery will be utilized with appropriate internal target volume (ITV) margins to account for respiratory movement.

The number of isocentres should be kept to a minimum, and it is suggested to utilize a single isocentre per body region whenever possible using volumetric modulated arc therapy (VMAT) or intensity-modulated radiotherapy (IMRT) to allow simultaneous treatment of multiple lesions. However, treatment using multiple isocentres is permitted with a limit of three isocentres per treatment day (nine per fraction) if needed for optimal target coverage.

##### Volume definitions

The gross tumor volume (GTV) will be defined as the visible tumor on imaging for all lesions. No additional margin will be added for microscopic spread of disease (i.e. Clinical Target Volume (CTV) = GTV), including for vertebral body metastases. For targets expected to be impacted by respiratory motion, an ITV may be created. The Planning Target Volume (PTV) will be between 2 mm and 5 mm depending on the site of disease, immobilization and set-up accuracy.

##### Treatment planning

Treatment planning will be performed using the fast helical CT simulation scan, with all OARs contoured. If needed, the 4D dataset may be used for planning tumours in the thorax and abdomen (using the untagged or a subset average depending on the motion assessment). Dose constraints may not be exceeded under any circumstance. There is no prespecified conformity index to be used. No hot spots (> 115%) are allowed outside of the PTV, and hot spots greater than 115% are only permitted with an exemption from the study principal investigator.

The target coverage goals are listed in Table 1. Should the radiation treatment plan not meet the targets below (i.e. falls into “not acceptable” category), the patient will be considered a treatment planning failure and will not be considered for entry into the 3 + 3 dose escalation study. The patient will then be planned at the next highest dose level where an acceptable radiation treatment plan can be generated and followed per the study protocol to assess toxicity. The tumours treated on any treatment day should meet target coverage goals from the isocentres delivered on that treatment day independently of the composite total dose.

**Table 1 Tab1:** Target coverage goals for the gross tumour volume (GTV) and planning target volume (PTV) on the ARREST clinical trial

**Goal**	**Acceptable**	**Not acceptable**
PTV: ≥95% of the PTV to receive ≥95% of the prescription dose for every lesion.	**GTV**: ≥95% of the GTV to receive ≥95% of the prescription dose for every lesion.	1. Failure to meet dose constraints listed in Additional file 1 2. Not being able to meet minimum “Acceptable” coverage for every lesion i.e. 3. < 90% of lesions meet the “Goal” target coverage criteria

##### Quality assurance

Each patient will have their treatment plan peer-reviewed by another radiation oncologist or at quality assurance rounds. The dose to each organ at risk must be verified by the treating physician or physicist to ensure doses to OARs are within acceptable limits. Dose delivery for VMAT or IMRT treatment plans will be confirmed prior to treatment by medical physics.

##### Special considerations during radiotherapy delivery

Given the large volume irradiated, pre-treatment with anti-emetics is mandatory for all patients on this study. The preferred treatment regimen will be ondansetron 8 mg 1–2 h prior to each radiotherapy fraction.

Patients are required to have bloodwork demonstrating adequate bone marrow function prior to delivery of the second fraction of radiotherapy, and every fraction thereafter. It is suggested this bloodwork be taken either after the last treatment of the previous level or on the first day of the next dose level, and reviewed by the treating oncologist prior to delivery of the next dose level of radiotherapy treatments. One repeat draw of bloodwork is permitted if the bloodwork values are just below the thresholds listed below. Criteria for stopping radiotherapy due to concerns of inadequate bone marrow function will be: CTCAE grade 3 anemia (hemoglobin less than 80 or symptomatic requiring a transfusion); CTCAE grade 3 thrombocytopenia (platelets less than 50), CTCAE grade 3 neutropenia (absolute neutrophil count less than 1).

Patients are not allowed to receive cytotoxic, immunotherapeutic or molecularly targeted agents within a time period commencing 2 weeks prior to initiation of radiotherapy until 6 weeks after completion of therapy. Patients on conventional hormone therapy (i.e. anti-estrogen or anti-testosterone therapy) may continue these medications.

